##### Process evaluation

A mixed-methods process evaluation will be conducted using the framework developed by Grant et al. [58]. The process evaluation aims to understand the trial delivery, implementation context, and participant engagement. We will use purposive sampling to select participants from each intervention arm and across study sites to ensure that all subgroups are represented.

Under trial delivery, we will assess the reach, fidelity, dose, and adherence to the intervention. Reach will be measured using the proportion of eligible participants, the proportion that consented, drop-outs, and representativeness by demographic characteristics. Fidelity, dose of, and adherence to the face-to-face element will be assessed using a self-report questionnaire, attendance sheets, observation, and audio ratings of selected sessions, and in-depth interviews with lay providers (*n* = 10) and supervisors (*n* = 3). Fidelity, dose of, and adherence to the digital element will be assessed using error reports, app log files (e.g., number and duration of completed EMA and EMI enhancing, consolidating, and interactive exercises). Where feasible, participants who discontinue the intervention will also be invited to provide feedback.

For the implementation context, we will qualitatively assess the need for adaptation, barriers, enablers, and contextual factors (structural, environmental, and cultural) that may influence implementation and outcomes. For engagement, participants will fill in a feedback questionnaire about their experiences post-intervention. In-depth interviews (IDIs) and focus group discussions (FGDs) will be conducted with a purposive sample of young people (*n* = 20) from the three intervention arms.

##### Acceptability, desirability, usability, and safety

Acceptability and usability of the digital element will be assessed using the Extended Unified Theory of Acceptance and Use of Technology (UTAUT2) [59] and the 21-item mHealth App Usability Questionnaire (e.g., MAUQ) [60]. For the acceptability and desirability of the face-to-face and digital element, we will conduct in-depth interviews with 30 participants (10 from each intervention arm). We will assess safety through monitoring Serious Adverse Events (SAEs), defined as any untoward medical occurrence that results in death, is life-threatening, requires hospitalization, or results in significant disability. SAEs will be documented and reported to the ethics committees and regulatory bodies using standardized reporting forms and protocols [61]. Given the brief, guided nature of the psychosocial exercises and close facilitator supervision, the risk of SAEs is expected to be very low. Risks will be monitored through ongoing observation by trained facilitators and assessors, participant self-report, and brief check-ins after face-to-face sessions. Participants showing distress and those needing additional support will be referred to clinical psychologists or appropriate mental health services. Participation may be paused if continued involvement poses risk.

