### Goals and hypotheses

This study has three specific goals:

Test the efficacy of the blended intervention, MAISHA, on ER difficulties (primary outcome) among young people in Kenya. We hypothesize that participants allocated to the blended intervention condition (digital + face-to-face) will exhibit lower levels of ER difficulties compared to those in the control condition (CAU) at the post-intervention stage.Examine the signals of efficacy of the blended intervention on secondary mental health outcomes. We hypothesize that participants assigned to the blended intervention will show higher positive affect, more adaptive emotion beliefs, and greater use of adaptive ER strategies, as well as lower negative affect, emotional reactivity, and symptoms of depression, anxiety, and stress compared to CAU. We will also compare the three intervention conditions with each other to explore the potential contribution of intervention elements to the overall effects.Assess the acceptability, desirability, usability, and safety of the blended mental health intervention components. We postulate that the blended intervention will be culturally acceptable, desirable, usable, and safe for participants.Investigate proximal signals of efficacy of momentary intervention components of the digital element. We hypothesize that these intervention components will lead to short-term improvements in momentary negative affect and ER difficulties. Using a micro-randomized trial nested within study arms that include the digital element, we will also explore when, under what conditions, and for whom specific components are effective.

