#### Control condition (Care as Usual)

CAU is broadly defined and includes standard health care services available within the public health system. This includes promotion, prevention, treatment, and rehabilitation of Mental, Neurological, and Substance Use (MNS) disorders for adolescents [40]. CAU is not actively monitored. All interventions will be given in addition to CAU. The control condition will also be put on a waiting list to receive an adjusted version of the digital element after the trial is finished.

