### Outcome measures

#### Primary outcomes

The primary outcome will be ER difficulties at post-intervention, while controlling for baseline differences, assessed with the DERS-SF [38] (see Table 1). The DERS-SF is a validated self-report measure with 18 questions organized in six subscales and rated on a 5-point Likert scale. DERS-SF demonstrates good internal consistency (α = 0.89) [38] and acceptable test-retest reliability (*r* = 0.67) [45]. The total sum score across all subscales will be compared between the blended intervention and the control condition.

**Table 1 Tab1:** An overview of measures and time points

Time points				
**Construct**	**Measures/Tools**	**Screening and Baseline (T0)**	**Throughout the intervention phase (T1)**	**Post-intervention (T2)**
*Screening measures*				
Sociodemographic characteristics	Demographic health survey questions on gender, age, education level, family economic status, and residence	X		
Functioning	Social and Occupational Functioning Assessment Scale (SOFAS) (63)	X		
Suicidality, Substance Use, Wellbeing	Community Quick Screening Tool (CQST) (66)	X		
*Primary outcome (Non-momentary)*				
Difficulties in Emotion Regulation	Difficulties in Emotion Regulation Scale (DERS-SF) (43)	X		X
*Secondary outcomes (Non-momentary)*				
Depression, anxiety, and stress	Depression Anxiety Stress Scale (DASS-21) (46)	X		X
Emotion Regulation	Emotion Beliefs Questionnaire (EBQ)(48)	X		X
	Emotion Regulation Questionnaire (ERQ)(49)	X		X
	Interpersonal Emotion Regulation Questionnaire (IERQ)(50)	X		X
Emotional reactivity	Short form of the Perth Emotional Reactivity Scale (PERS-S)(47)	X		X
Positive and negative affect	Positive And Negative Affect Schedule (PANAS)(45)	X		X
*Secondary outcomes (momentary)*				
Difficulties in Emotion Regulation	Eight alternating items of the State Difficulties in Emotion Regulation Scale (S-DERS)(56)		X	
Affect valence and arousal	Four bipolar VAS and one multiple-choice EMA item		X	
Event-related stress	Two VAS items assessing occurrence and intensity		X	
Emotion regulation capacity	Two alternating VAS items		X	
Social context	Two multiple-choice items		X	
Activities	One multiple-choice item		X	
Perceived Emotion regulation success (only Post-EMI EMA)	One VAS item		X	
Sleep quality (only morning check-in)	One VAS item		X	
Expectation about the day (only morning check-in)	One VAS item		X	
Reflection on the day (only evening check-in)	One VAS item		X	

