*Process evaluation*,* Acceptability*,* Desirability*,* Usability*,* and Safety*				
Usability: digital element	MAUQ(59)			X
Acceptability: digital element	Unified Theory of Acceptance and Use of Technology (UTAUT)(67)			X
Acceptability and Desirability: digital and face-to-face element	Self-report questionnaire, In-depth interviews			X
Safety	Monitoring of SAEs		X	
YPAR experiences	Survey, reflective diaries, and in-depth interviews		X	X
Process evaluation: Trial delivery	Self-report questionnaire, attendance sheets, observation/audio ratings of selected sessions, in-depth interviews		X	X
Process evaluation: Implementation context	In-depth interviews			X
Process evaluation: Engagement	Self-report questionnaire, in-depth interviews, and FGDs			X

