Secondary measures - including positive and negative affect, symptoms of depression, anxiety, and stress, emotional reactivity, emotion beliefs, ER strategies, and interpersonal ER - will be analyzed using mixed-effects linear regression models, consistent with the approach described for the primary analysis. Exploratory analyses comparing the other intervention conditions (e.g., face-to-face and digital only against CAU) will be conducted to explore the potential contribution of intervention elements to overall effects and generate hypotheses for future implementation.

Exploratory analyses will include subgroup analysis to examine whether signals of efficacy of the blended intervention differ across specific groups. These analyses will be conducted within the primary mixed-effects model using interaction terms. We will examine proximal signals of efficacy of digital intervention components using data from the micro-randomized trial. Mixed-effects linear regression models with EMA observations (level 1) nested within individuals (level 2) will be applied to account for the hierarchical structure of longitudinal EMA data. Variables will include momentary negative affect, stress, and momentary ER. EMA data before and after momentary intervention components will be compared and types of EMI exercises (i.e., breathing, imagery, diary, control) will be included as independent variables. Results from all exploratory analyses will be interpreted using effect sizes and 95% confidence intervals rather than formal significance testing. Data from the process evaluation, acceptability, desirability, usability, and safety, sample characteristics, and baseline measures will be summarized descriptively.

We assume data will be Missing at Random (MAR) and will explore missingness patterns to assess this assumption. Continuous variables will be presented using means and standard deviations or medians and interquartile ranges; categorical variables using frequencies and percentages. All statistical analyses will be conducted in R.

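### The only stated safety measure is a rare-event count that can say little at this sample size, while individual worsening on scales already collected is not used as a harm outcome

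*Protocol article*

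**What the plan says.** In the section on acceptability, desirability, usability and safety, the article defines the safety assessment: "We will assess safety through monitoring Serious Adverse Events (SAEs), defined as any untoward medical occurrence that results in death, is life-threatening, requires hospitalization", with significant disability as the last criterion. In Table 1 the entry for safety is "Monitoring of SAEs", marked for the intervention phase only, and nothing else is listed against safety.

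The same section says that "the risk of SAEs is expected to be very low". It also describes day-to-day oversight: "Risks will be monitored through ongoing observation by trained facilitators and assessors, participant self-report, and brief check-ins after face-to-face sessions". Distressed participants may be referred, and participation may be paused. None of this is named as an outcome. Under the control condition the article says "CAU is not actively monitored".

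The goals section states the expectation: "We postulate that the blended intervention will be culturally acceptable, desirable, usable, and safe for participants". No threshold, margin or comparator is attached to the word *safe*. The quantitative analysis section says how the data will be handled: "Data from the process evaluation, acceptability, desirability, usability, and safety, sample characteristics, and baseline measures will be summarized descriptively".

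DASS-21 and DERS-SF are scheduled in Table 1 at baseline and post-intervention, with no restriction by arm. The analysis section uses them as efficacy outcomes in mixed-effects linear models of the post-intervention score.

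**The concern.** The plan pairs an expectation of safety with a single measure that it predicts will be almost empty. If SAEs are as rare as expected, an arm of this size will often record none, whether or not the intervention makes some participants worse. A reader of the final report could then take an empty table as support for the safety expectation, although it would carry little information.

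The gap matters because the harm most plausible in an indicated sample of young people with emotion regulation difficulties is a worsening of symptoms that stops short of death, threat to life, hospitalisation or disability. The trial already measures symptoms and regulation difficulties before and after the intervention. A mean can improve while a minority deteriorates, and a comparison of means does not report how many did.

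**Working it through.** **Inputs.** From the quantitative data section: 25 clusters of 6 per arm, so 150 analysed per arm and 600 in total; ICC 0.05; detectable difference 0.36; 10% dropout; 666 recruited, or about 166 per arm. From the primary outcome section: DERS-SF test-retest r = 0.67. The article gives no SAE rate and no deterioration rate, so every such rate below is an assumption.

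**The plan's own figures.** Design effect = 1 + (6 − 1) × 0.05 = 1.25. Effective n per arm = 150 / 1.25 = 120. Reading 0.36 as SD units, with a two-sided 5% test, power is 79.6% (78.0% using t with 48 df), against 80% stated. Recruitment = 600 / 0.9 = 666.7, against 666 stated. Both agree closely enough that 150 and 166 per arm can be used here.

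**What zero SAEs would show.** The one-sided 95% upper limit for 0 events in n is 1 − 0.05^(1/n).
- n = 150: 2.0%
- n = 166: 1.8%

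The upper ends of the two-sided exact 95% intervals, 1 − 0.025^(1/n), are 2.4% and 2.2%.

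**How often the blended arm would show none.** P(0 events) = (1 − p)^n.

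| Assumed true SAE rate | n = 150 | n = 166 |
|---|---|---|
| 0.1% | 0.86 | 0.85 |
| 0.2% | 0.74 | 0.72 |
| 0.5% | 0.47 | 0.44 |
| 1% | 0.22 | 0.19 |
| 2% | 0.05 | 0.03 |

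**Comparison with care as usual.** With 150 per arm, Fisher's exact test gives p = 0.060 for 5 versus 0 events and p = 0.030 for 6 versus 0. Power to separate 0.5% from 2% is about 4%, and 0.5% from 3% about 17%. The article plans no such test; these figures only show how little the count can discriminate.

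**What individual worsening could show.** With 150 per arm and design effect 1.25, assuming 10% versus 5% worsen:

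95% half-width = 1.96 × √[(0.10 × 0.90 + 0.05 × 0.95) / 150 × 1.25] = 0.066.

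The interval would be about 5 ± 6.6 points, or −1.6 to 11.6. At 5% versus 15%, power is 83% ignoring clustering and 74% after the design effect. At 10% versus 20% it is 68% and 58%. The ICC is the plan's value for a continuous score, borrowed here for a binary outcome.

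**Size of a reliable-change threshold.** With r = 0.67, the conventional cut-off is 1.96 × √[2 × (1 − 0.67)] = 1.96 × √0.66 ≈ 1.6 SD. That is a large change.

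**The case against.** Several counter-arguments carry weight.

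A reader might infer that the safety expectation cannot fail. The figures do not support that: at assumed rates of 0.5% and 1%, the chance of at least one SAE among 166 is 1 − 0.44 = 0.56 and 1 − 0.19 = 0.81. The accurate statement is that no criterion is given and the count is weakly informative.

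A reader might also take the goal as a formal test. The text speaks of assessing and postulating, and the analysis is descriptive.

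Nor does the article say that referrals or pauses will be left out of the report. It describes oversight under the safety heading without stating that the results are outcomes, so exclusion is an inference.

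Worsening is not ignored altogether: average harm would appear in the planned models as a difference in the wrong direction. Only individual deterioration is missing.

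The article promises a detailed statistical analysis plan, which could add a deterioration analysis, and an article condenses a fuller protocol. This is fair and limits the point to what is stated: a safety measure defined as SAEs alone, beside an unqualified expectation of safety.

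Finally, the alternative is imprecise too. At 10% versus 5% the interval includes zero, and power is only about 31% after the design effect. In a sample selected for high scores, where the article itself anticipates regression to the mean, worsening by 1.6 SD may be rare. These limits stand, but the comparison still uses the same questionnaires in every arm.

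**Conclusion.** The concern holds in a limited form. The only safety measure the article names is the SAE count, which it expects to be close to empty, and the safety expectation has no criterion. Zero events in the blended arm would leave true rates up to about 1.8% to 2.0% open (one-sided 95%, for 166 and 150 participants). Individual deterioration on DASS-21 and DERS-SF is not used as a harm outcome, although the data will exist.

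The upper limits rest only on the arm size and a binomial model without clustering. The probabilities of no event, the powers and the ±6.6 points rest on assumed rates, and the last also on the plan's ICC of 0.05.

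Two further readings are not supported. Table 1 marks the tool for "Suicidality, Substance Use, Wellbeing" at screening and baseline only, from which a reader might infer that it must be repeated; it is listed as a screening measure, and the point does not depend on it. A reader might also expect referral or pause counts to serve as a harm comparison between arms. They would not do so fairly: check-ins follow face-to-face sessions, so they exist only in the two arms with that element, and care as usual is not actively monitored.

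**What to change.** 1. Add a descriptive safety outcome: the number and proportion in each arm who worsen from baseline to post-intervention on DASS-21 and on DERS-SF by an amount fixed before the data are accessed. Give cluster-adjusted risk differences with 95% confidence intervals for each intervention arm against care as usual. In choosing the threshold, note that a reliable-change cut-off from the stated r = 0.67 is about 1.6 SD, and state that precision will be limited.
2. Report SAEs by arm with exact 95% confidence intervals, and reword the safety expectation so that an empty SAE table is not treated as evidence of safety.
3. Referrals, pauses and distress-related withdrawals may be listed descriptively, with a note that detection differs between arms. They should not be used as a between-arm comparison.

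Items 1 and 2 need no new data collection. Item 3 needs only a log of events that the procedures already generate. The cost is a few extra tables and a safety statement less favourable than a bare report of no SAEs.

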#### Face-to-face intervention element

Building on the Kenyan Shamiri intervention [11], the face-to-face element of maisha involves four group sessions grounded in the wise interventions framework [44]: growth mindset (sessions 1 and 2), gratitude (session 3), and value affirmation (session 4). The sessions will run weekly for 1 h over four weeks, delivered in small groups of 6 to 7 young people by lay providers (aged 18 to 22). Supervision (ratio of 1:5) will be provided by trained clinical psychologists (see Supplementary methods 2).

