#### Data collection

Measures will be assessed at two time points: baseline (i.e., before randomization, also used for screening) and post-intervention (i.e., after the 28-day intervention period). To assess primary and secondary outcomes, participants will complete self-report measures using *Redcap* [67], a secure electronic data capture system with built-in quality control features (e.g., logic checks), and participate in interviews and FGDs (see Table 1 - Additional File 2). All data collection tools will be administered in English.

During the intervention phase, participants assigned to the digital or blended intervention arms will receive four mood checks daily with two alternating EMA item sets each day, scheduled at random within set blocks of time. For proximal effects assessment, participants will be prompted to reply to a post-EMI EMA with three items after each momentary intervention component. Morning and evening EMA will be collected at participant-defined times. A research team member will routinely review incoming data for completeness and consistency. Additional data cleaning steps will be performed before analysis to ensure data integrity.

Qualitative data collection will follow the principle of information power, i.e., stopping at the point at which no new information is obtained and redundancy is reached [68]. If possible, interviews will be conducted face-to-face.

Data collection will be conducted by a research team consisting of a PI, co-investigators, doctoral students, youth researchers, and local researchers. The data collection team will be fluent in English with experience in using both quantitative and qualitative methodologies.

The feasibility of all tools, including EMA, was piloted in the co-design phase with adolescents and young people who tested the questionnaires, EMA, and EMI over 2 weeks. Their feedback indicated that the number and frequency of items were manageable. Based on this pilot, several adaptations were implemented to further reduce participant burden, such as allowing users to adjust prompt times and enabling a ‘do-not-disturb’ mode.

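### No harm enquiry common to all four arms is stated, so a descriptive SAE table by arm would rest on unequal ascertainment

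*Protocol article*

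**What the plan says.** Under Goals and hypotheses, safety is part of a stated goal: "We postulate that the blended intervention will be culturally acceptable, desirable, usable, and safe for participants". No comparator is named.

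Under Acceptability, desirability, usability, and safety, the measure is SAEs: "We will assess safety through monitoring Serious Adverse Events (SAEs"), defined by death, threat to life, hospital admission or significant disability. The same section gives the channels: "Risks will be monitored through ongoing observation by trained facilitators and assessors, participant self-report, and brief check-ins after face-to-face sessions".

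In Table 1 the Safety row reads "Monitoring of SAEs". Its single mark is in the column headed "Throughout the intervention phase (T1"). The T2 cell is empty, although the rows just below it, for the participatory research experience and for trial delivery, are marked in both columns.

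Contact between baseline and T2 differs by arm:
- **Arms A and C** have group sessions: "The sessions will run weekly for 1 h over four weeks, delivered in small groups of 6 to 7 young people by lay providers" (Face-to-face intervention element).
- **Arms A and B** have the app: "participants assigned to the digital or blended intervention arms will receive four mood checks daily" (Data collection).
- **Arm D** has no scheduled contact until T2, defined as "post-intervention (i.e., after the 28-day intervention period") in Data collection.

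The section Quantitative data says that safety data will be summarised descriptively.

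**The concern.** How many harms a trial records depends on how many occur and on how hard they are looked for. If the looking differs by arm, a difference in counts may reflect contact rather than risk. Here two of the named channels exist only where there are sessions, and the one contact that could treat all arms alike carries no safety mark.

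Two readings of the final report would then be unsafe. A higher count in A or C than in D could come from closer observation. A low count in B or D could come from nobody having asked.

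A second, smaller issue is that SAEs are the only named safety measure and are expected to be very rare. Worsening of symptoms, a plausible harm in young people selected for difficulties in emotion regulation, is not named as a safety outcome. Yet DASS-21 and DERS-SF are collected in every arm at baseline and T2.

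**Working it through.** **1. Channels against arms.** This sets the safety section beside the intervention and data collection sections.

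| Named channel | A blended | B digital | C face-to-face | D CAU |
|---|---|---|---|---|
| Facilitator observation | yes | no | yes | no |
| Check-in after session | up to 4 | none | up to 4 | none |
| Assessor observation | T0, T2 | T0, T2 | T0, T2 | T0, T2 |
| Participant self-report | route not described | route not described | route not described | route not described |

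The app adds contact in A and B, including an open-ended item. However, the Data collection section describes the review of incoming data as a check that they are complete and consistent, not as a search for harms. The chat supported by session leaders is described for the blended arm only. In D, an event between baseline and T2 would reach the trial through unprompted self-report, or by being mentioned at T2.

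**2. Timing.** T1 is the same 28 days in every arm and fills the interval between the two assessments. The window itself is therefore balanced. The gap is that no SAE enquiry about those 28 days is marked at T2.

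**3. Direction and possible size.** The article gives no SAE rate and no capture probability. Assume the same true risk p in A and D, 150 analysed per arm (25 clusters × 6, from Quantitative data), and full capture in A. With capture share s in D:

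- expected recorded events: A = 150p, D = 150ps
- apparent ratio A:D = 1/s

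| Assumed s | Ratio 1/s | Expected A : D at assumed p = 2% |
|---|---|---|
| 100% | 1 | 3.0 : 3.0 |
| 50% | 2 | 3.0 : 1.5 |
| 25% | 4 | 3.0 : 0.75 |

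The ratio only restates s. The design suggests the direction; the size is assumed.

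**4. What zero events would mean.** With no recorded SAE among 150, the one-sided 95% upper bound on the risk of a *recorded* event is 1 − 0.05^(1/150) = 0.0198, about 2.0%. Dividing by an assumed capture share gives the bound on true risk: 0.0198/0.5 = 4.0%, or 0.0198/0.25 = 7.9%. Clustering is ignored.

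**5. Would equal ascertainment allow a test?** No. At 150 per arm, two-sided 5%, ignoring clustering, the power of Fisher's exact test is about 2% for 1% against 2%, 10% for 1% against 3%, and 40% for 1% against 5%. These rates are assumed.

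**The case against.** The strongest case against has five parts.

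- **No comparison is planned.** The goal names no comparator and the analysis is descriptive. This stands. A reader might infer that the plan promises a safety test against CAU that it cannot deliver. It promises none, and step 5 shows that such a test would have little power even with perfect ascertainment. What remains is that a descriptive table by arm can still mislead.
- **Sessions are not the only route.** Assessors and self-report are not tied to sessions, so it would go too far to say that harms are sought mainly there. The imbalance comes from the two channels that are tied to sessions.
- **The T1 mark shows the period covered, not who is asked when.** This is partly right, and the period is the same in every arm. But other rows use both columns, and no text says that participants are asked about SAEs at T2.
- **SAE forms and procedures are cited but not shown, and the quoted sentence speaks of risks rather than SAE counts.** A fuller procedure may well include a common enquiry. It would then have to be reconciled with the channels and the time point that the article itself fixes.
- **Events this serious may become known anyway in a school class or community group.** This is plausible, and it is why no particular bias can be claimed. A reader might infer that the blended arm will appear two or three times less safe than CAU. The documents contain no figure from which that could be derived.

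On symptom worsening, the planned models for DASS-21 and DERS-SF would show an average deterioration. They would not show a minority who worsen while the mean improves.

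**Conclusion.** The point holds as a cheap improvement, not as a flaw in the trial's main comparison. The article states channels of harm detection that differ by arm and marks no safety enquiry at the shared T2 contact. Raw SAE counts by arm would therefore not be comparable, with a tendency to make A and C look worse than D. Few events in B or D would be weak evidence of safety.

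This rests on reading the article as it stands, with the full protocol and SAE procedure not at hand. The magnitude is unknown. The ratios of 2 and 4, and the bounds of 4.0% and 7.9%, are illustrations under assumed capture shares. The primary outcome analysis is unaffected.

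**What to change.** 1. Mark Safety at T2 as well as T1 in Table 1.
2. Put the same few SAE questions, covering the 28 days, on the T2 REDCap form for all four arms. Base any description by arm on this route, and give the number who answered in each arm, because the enquiry misses those who do not reach T2 (the plan allows for 10% dropout).
3. List events found through sessions, the app or other routes separately, with the route named.
4. Report descriptively by arm the proportion whose DASS-21 or DERS-SF score worsened from baseline to T2 by more than an amount set beforehand in the SAP.
5. If the SAE procedure already contains a common enquiry, say so in the safety section and in Table 1.

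The cost is a few extra T2 items and one descriptive table. Sample size, treatment and the primary analysis do not change. With very few SAEs the comparison stays descriptive.
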